**Background**

Sleep deprivation induces degradation of night-time driving ability via sleepiness. Because of conflicts between physiological needs and social or professional activities, it is necessary to develop affordable countermeasure to sleepiness. In real-life driving studies, nap and coffee are efficient countermeasures of sleepiness at the wheel. However the effect of caffeine is quick but brief and varies between individuals. There is a need for more knowledge in order to know what to recommend to drivers. Exposure to 460-nm monochromatic light (blue light) decreases subjective sleepiness and improves performances. One objective of this project is to investigate whether blue light exposure during driving would be useful in a real driving situation when sleepiness becomes acute. Owing to the fact that our knowledge of the effects of exercise on driving is very sparse and to the absolutely need to standardize the bouts of exercise that will be applied to the subjects. One objective of the present study will be to investigate in a simulator study the effects of a bout of moderate exercise on participants driving ability when sleepiness becomes acute. Nocturnal neurobehavioral performance varies widely between individuals and only certain subjects seem significantly affected by sleep loss. It is of interest to find biological markers for sleep drive to identify vulnerable drivers to sleep deprivation or to identify responders to sleepiness countermeasures (i.e., coffee and blue light). One objective of this study is to determine individual differences (genetic, hormonal and cognitive) in the impairment of driving skills induced by sleep loss and in the efficiency of countermeasures (blue light and coffee).

**Study objectives**

Primary objective

To compare the effects of continuous blue light exposure during driving with those of coffee (2*200 mg of caffeine) and coffee placebo on 4h night-time driving performance in young (20-25 years) and middle-aged (40-50 years) healthy volunteers

Secondary objectives

To determine the effect of age in the effectiveness of countermeasures (blue light and coffee)

To determine individual differences (cognitive, genetic and hormonal) in the impairment of neurobehavioral functions from sleep loss and in the effectiveness of countermeasures (blue light and coffee)

To determine the effects of blue light on quality and quantity of sleep after night-time driving in young and middle-aged healthy volunteers

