**Study design**

Experimental design

This is an interventional study: Double-blind (except for blue-light), Randomized, Crossover, Comparative versus referent countermeasure of sleepiness: coffee (2*200 mg of caffeine) and placebo.

The study is divided into the following periods:

1. **selection period** without treatment between selection and inclusion visits to check the absence of exclusion criteria with questionnaires, polygraphic recording (respiratory sleep disorders and periodic leg movements) and actimetry (sleep efficiency, total sleep time)
2. **acute treatment period**, each volunteer will be randomly allocated to successively and randomly receive either continuous blue light exposure or 2*200 mg of caffeine or placebo of caffeine during night driving with at least 1 week between treatment.

Experimental protocol

SELECTION

Participant will complete the French version of the Basic Nordic Sleep Questionnaire (BNSQ), the self-report symptoms inventory SCL-90R, the chronotype questionnaire of Horne and Ostberg, the Epworth sleepiness scale. They will to have 7 consecutive days monitoring using actimeters and 1 night using polygraph.

INCLUSION

Participants will be screened for eligibility criteria. They will sign informed consent, perform cognitive tests, complete the caffeine sensitivity questionnaire. Blood samples will be collected.

DRIVING SESSION

Each subject, will come at the laboratory at 9:30 PM, and will kept awake until the time of the experimental session.

For each driving session (Blue light, caffeine and placebo of caffeine), all participants will drive 400 km (250 miles) on the same 2-lane highway for 4 hours. After 2 hours of driving (200 km, 125 miles) subjects will take a 15-minutes break. The night-time driving session will start at 1:00 AM and Stop at 5:15 AM. At the beginning, middle and end of the driving, participants will be asked to rate their instantaneous fatigue and sleepiness. After driving, sleep recuperation will be recorded in laboratory during a minimum of 6h. Saliva will be collected before and after the driving session and after sleep recuperation.

The subjects were instructed to maintain a regular sleep-wake schedule and were monitored by actimetry during the 3 days preceding each experimental session and during the 3 days after each experimental session.

**
[figure not shown]
**

C: Coffee

P: Placebo

BL: Blue Light

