**Expected results**

- Improvement of nocturnal driving ability with countermeasures to sleepiness (coffee and continue blue light exposure) versus placebo in young and middle-aged healthy volunteers.

- Same beneficial effect of continue blue light exposure versus coffee on nocturnal driving ability in young and middle-aged healthy volunteers.

- Characterization of biological (genetic, cognitive or hormonal) markers explaining inter-individual variability in nocturnal driving impairment and effectiveness of countermeasures to sleepiness.

- Modifications on quality and quantity of sleep after the blue light exposure during nighttime driving in young and middle-aged healthy volunteers.

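### No driving outcome is measured in a rested state, so the impairment half of the second secondary objective cannot be identified; it should be restated as night-time performance

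*Protocol*

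**What the plan says.** **Objective.** Protocol, Study objectives, second secondary objective: "To determine individual differences (cognitive, genetic and hormonal) in the impairment of neurobehavioral functions from sleep loss", joined to a second half on the effectiveness of blue light and coffee. The Background gives the motive, "It is of interest to find biological markers for sleep drive to identify vulnerable drivers to sleep deprivation", and there names driving skills as the function impaired. Expected results promises "markers explaining inter-individual variability in nocturnal driving impairment".

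**Measurement.** Study design describes three driving sessions: blue light, caffeine and caffeine placebo. Participants arrive at 9:30 PM and "will kept awake until the time of the experimental session". "The night-time driving session will start at 1:00 AM and Stop at 5:15 AM". Clinical assessment methods mentions a training session but gives it no time of day and no recorded outcome. The design figure is not available to us; its legend lists only coffee, placebo and blue light.

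**Predictors.** At inclusion participants "perform cognitive tests, complete the caffeine sensitivity questionnaire". Criteria of assessment lists cognitive results, polymorphisms, chronotype and saliva measures as secondary criteria, apart from the efficacy criteria.

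**Analysis.** Analyses of variables models the number of crossings per participant by negative binomial regression on treatment and on age or type. Lateral-position SD is analysed by two-way ANOVA pairing age, genotype, hormonal type or cognitive type with treatment. No rested value appears in either model.

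**The concern.** Impairment from sleep loss, for one driver, is his performance when sleep-deprived minus his performance when rested. The trial records only the first term. A man with many crossings or a wide lateral-position SD on the placebo night may drive in much the same way by day. A genotype or cognitive type associated with the night value could therefore mark ordinary driving ability and still be reported as a marker of vulnerability to sleep loss, which is the use the Background has in mind. An analysis plan could not repair this, because the rested value would never have been collected.

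**Working it through.** **1. What each planned contrast identifies.** Write driver i's rested level as S_i, his loss from being awake at night as V_i, and the effect of treatment t as T_it. Apart from noise, the observed values are:

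- placebo night: S_i + V_i
- treated night: S_i + V_i + T_it

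Treated minus placebo gives T_it, because S_i and V_i cancel. A type-by-treatment term against placebo therefore answers the countermeasure half. A type main effect, or a type difference on the placebo night, gives the difference in S + V. Separating V needs a value of S alone, and no planned measurement supplies it.

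**2. Could another measurement stand in for S?**

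- Training session: no stated time and no recorded outcome.
- Sleepiness and fatigue ratings: taken at the start, middle and end of the drive, so the first is at about 1:00 AM.
- Saliva: before and after the drive and after recovery sleep; not a driving outcome.
- Cognitive tests: at inclusion only, and used as a typing variable.
- First 200 km of the placebo drive: already after 1:00 AM.

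None is a rested driving value.

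**3. Size, on assumptions.** The documents give neither the habitual share of between-driver variance nor any marker correlation. Assume a share h and a marker correlated c with habitual style and 0 with vulnerability. The correlation with the placebo-night score is r = c × √h. The chance of a significant result at two-sided 5% is approximately Φ(atanh(r) × √(n − 3) − 1.96), plus a small opposite tail, with n = 48 (Determination of sample size) and √45 = 6.708.

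At h = 0.5:

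| c | r | atanh(r) × 6.708 | chance of a false marker |
|---|---|---|---|
| 0.1 | 0.071 | 0.475 | about 8% |
| 0.2 | 0.141 | 0.955 | about 16% |
| 0.3 | 0.212 | 1.445 | about 30% |
| 0.5 | 0.354 | 2.479 | about 70% |

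Holding c = 0.5 and varying h over 0.25, 0.5 and 0.75 gives r = 0.25, 0.354 and 0.433, and about 40%, 70% and 88%. The nominal rate is 5%.

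**4. Second illustration, also on assumed values.** A simulation used 24 against 24 drivers by marker on a log scale, with skill SD 0.6, vulnerability SD 0.6, noise SD 0.3 and 4000 runs. The marker shifted rested skill only.

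| shift in rested skill | night value alone: significant | night minus rested: significant |
|---|---|---|
| 0 | 4.9% | 5.1% |
| 0.25 | 15% | 4.6% |
| 0.5 | 46% | 5.3% |
| 0.75 | 82% | 5.4% |

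Subtracting a rested value holds the error near 5%; the night value alone does not. These shifts are large: 0.5/0.6 is about 0.8 of a skill SD. Both illustrations use a continuous score, whereas crossings are counts analysed over all treatments by negative binomial regression. They show direction and range and are not estimates for this trial.

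**The case against.** **Crossings may need no rested reference.** The protocol excludes overtaking and traffic-related deviations so that crossings reflect driver status, and it provides for cells with no crossings at all. If rested counts are near zero, the placebo-night count is close to the change. This weakens the point for crossings but does not settle it, because no rested count is given. It does not help lateral-position SD, which is not near zero at rest and which the protocol itself treats as representing overall highway driving ability.

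**The named ANOVA terms pair type with treatment.** Those interactions address the countermeasure half, which stands. Misattribution arises only where a type main effect is read as vulnerability. But the objective, the Background and the expected result invite that reading, and the crossings model enters type as a determinant in its own right.

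**Inclusion-only cognitive testing.** A reader might infer from "They will sign informed consent, perform cognitive tests, complete the caffeine sensitivity questionnaire" that the tests should have been repeated after sleep loss. The documents do not support this. The tests come under subject typing, are listed apart from the efficacy criteria and enter the models as cognitive type. They are predictors, for which one measurement at inclusion is appropriate, and the Background names driving skills as the outcome.

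**Only half of one secondary objective is affected.** This is true, and it limits the importance of the point. It does not make the present wording supportable.

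**Conclusion.** The point holds in a limited form. The impairment half of the second secondary objective, and the matching expected result, cannot be answered by this design because no driving outcome is recorded in a rested state. This follows from the protocol's own schedule and rests on no numerical assumption; the one caveat is the missing design figure, whose legend nevertheless names no rested condition.

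The size of the resulting error cannot be determined from the documents. With a 50% habitual share and marker correlations of 0.1 to 0.5, the false-marker chance runs from about 8% to 70%. A reader might take the upper figure as the expected error. It requires a marker explaining 25% of habitual style (0.5² = 0.25) and nothing of vulnerability, for which the protocol offers no support.

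The concern is stronger for lateral-position SD than for crossings. It does not reach the countermeasure half, where each man's placebo night is a valid reference, or the primary comparison.

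**What to change.** Restate the second secondary objective and the matching expected result as individual differences in night-time driving performance on placebo and in response to blue light and coffee. State that type main effects on crossings or lateral-position SD will not be interpreted as vulnerability to sleep loss or as impairment relative to rest. Adjust the Background sentences on vulnerable drivers and impaired driving skills to match.

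A contrast of the second with the first 200 km of the placebo session may be reported, but only as exploratory within-drive deterioration. Both halves fall after 1:00 AM, and time on task, time awake and the break (with its second placebo drink) are confounded, so it does not measure impairment from sleep loss.

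The cost is a change of wording and a narrower claim; no new data are needed. Keeping the present claim would require a rested drive on the same route with the same outcomes recorded, at greater cost.

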**Study design**

Experimental design

This is an interventional study: Double-blind (except for blue-light), Randomized, Crossover, Comparative versus referent countermeasure of sleepiness: coffee (2*200 mg of caffeine) and placebo.

The study is divided into the following periods:

1. **selection period** without treatment between selection and inclusion visits to check the absence of exclusion criteria with questionnaires, polygraphic recording (respiratory sleep disorders and periodic leg movements) and actimetry (sleep efficiency, total sleep time)
2. **acute treatment period**, each volunteer will be randomly allocated to successively and randomly receive either continuous blue light exposure or 2*200 mg of caffeine or placebo of caffeine during night driving with at least 1 week between treatment.

Experimental protocol

SELECTION

Participant will complete the French version of the Basic Nordic Sleep Questionnaire (BNSQ), the self-report symptoms inventory SCL-90R, the chronotype questionnaire of Horne and Ostberg, the Epworth sleepiness scale. They will to have 7 consecutive days monitoring using actimeters and 1 night using polygraph.

INCLUSION

Participants will be screened for eligibility criteria. They will sign informed consent, perform cognitive tests, complete the caffeine sensitivity questionnaire. Blood samples will be collected.

DRIVING SESSION

Each subject, will come at the laboratory at 9:30 PM, and will kept awake until the time of the experimental session.

For each driving session (Blue light, caffeine and placebo of caffeine), all participants will drive 400 km (250 miles) on the same 2-lane highway for 4 hours. After 2 hours of driving (200 km, 125 miles) subjects will take a 15-minutes break. The night-time driving session will start at 1:00 AM and Stop at 5:15 AM. At the beginning, middle and end of the driving, participants will be asked to rate their instantaneous fatigue and sleepiness. After driving, sleep recuperation will be recorded in laboratory during a minimum of 6h. Saliva will be collected before and after the driving session and after sleep recuperation.

The subjects were instructed to maintain a regular sleep-wake schedule and were monitored by actimetry during the 3 days preceding each experimental session and during the 3 days after each experimental session.

**
[figure not shown]
**

C: Coffee

P: Placebo

BL: Blue Light

**Selection of participants**

Inclusion criteria

- Healthy volunteers
- Aged between 20-25 years or 40-50 years
- Male
- BMI between 18 and 27
- Moderate caffeine drinkers (2-3 cups by day)
- Non professional drivers had their driving license for at least 2 years and drove between 10000 and 20000 km per year
- Showing a morning or evening chronotype (Horne questionnaire score >58 or < 42 for young subjects and Horne questionnaire score >64 or < 53 for middle-aged subjects)

The patient’s informed consent must be obtained at the inclusion.

Exclusion criteria

- Evidence of psychopathology (self-reports symptom inventory SCL-90R score >59 on the general symptomatic index and the following symptom dimensions: depression, anxiety, paranoid ideation and psychoticism)
- Evidence of sleep disorders (Items of Basic Nordic Sleep Questionnaire >3),
- Evidence of excessive daytime sleepiness (Epworth sleepiness scale score >9)
- Hypopnea-apnea index ≥ 5 (assessed by polygraphy)
- Periodic leg movement index ≥ 15 (assessed by polygraphy)
- Sleep efficiency < 85 % (assessed by actimetry during 7 consecutive days)
- Shift-workers and jet-lag the month before their inclusion in the study
- Severe controlled or uncontrolled diseases (psychiatric disorders, neurological disorders, sleep disorders, hepatic or renal failure, unstabilized diabetes, neoplasic disorders, cardiovascular disorders, pulmonary disorders, digestive disorders,…)

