Cognitive speed

- The Trail Making Test (TMT) R. Reitan, Trail Making Test: manual for administration and scoring, Reitan Neuropsychology Laboratory, Tuscon, AZ (1992) is used to assess cognitive speed, visual motor tracking, divided attention, and mental flexibility. It consists of two parts. In Part A, the participant has to connect numbers from 1 to 25 in the correct order as fast as possible (cognitive speed and visual motor tracking). (Pen and paper test). The score was total duration in seconds and the number of correct moves.

- The Digit Symbol subset of the WAIS-R is used to measure coding ability. This test is a performance measure which requires the subject to code nine simple symbols matched with nine numerals. The subject is given 90 seconds to code all items on the test. (Pen and paper test)

Flexibility

- TMT-B : numbers from 1 to 13 and letters from A to M must be connected in alternating fashion, beginning at 1-A and ending at M-13. Total score is given by time spent to complete each part (Pen and paper test)

- TEA Flexibility : Two stimuli (letter and digit) are displayed at a time. Subjects will be instructed to push on right or left key in according to the target. (Computerized test)

Working Memory

Updating memory task. Subjects must recall digit number list.

SELECTION

Actigraphy

Actimeters will be used to quantify our volunteers’ sleep duration and quality. This device monitors body movements and allows calculation of mean nocturnal sleep episodes and of nocturnal awakenings. Time in bed will be also computed as the time difference between going to bed in the evening and getting up in the morning. Sleep efficiency will be calculated as the ratio of time asleep to the time in bed, in percentage. To rule out any sleep-wake schedule disorders each subject will be monitored for 7 days before being included in the study. Subjects will be included if they have a mean sleep efficiency of at least 85% during the 7 days of recordings.

Polygraphy

A nocturnal polygraphy (nasal flow, oxygen saturation, two respiratory effort belts, snore, position, leg movement) will be performed to eliminate subjects suffering from sleep disorders. Subjects presenting an AHI > 5 for the 20-25 years old and > 10 for the 40-50 years old or a PLM index >15 will be excluded of study.

Habitual sleep patterns

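### The only consent step in the protocol text is at the inclusion visit, after the selection questionnaires, actimetry and polygraphy; it belongs at the selection visit

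*Protocol*

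**What the plan says.** Study design (Experimental design) describes a selection period "without treatment between selection and inclusion visits to check the absence of exclusion criteria with questionnaires, polygraphic recording" and actimetry. Selection and inclusion are therefore two visits, with study procedures between them.

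Study design (Experimental protocol) then lists what happens at each step:

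- **Selection.** "Participant will complete the French version of the Basic Nordic Sleep Questionnaire (BNSQ), the self-report symptoms inventory SCL-90R", together with the Horne and Ostberg chronotype questionnaire and the Epworth scale. Of the recordings it says: "They will to have 7 consecutive days monitoring using actimeters and 1 night using polygraph".
- **Inclusion.** Eligibility is checked, and then: "They will sign informed consent, perform cognitive tests, complete the caffeine sensitivity questionnaire". Blood is also taken at this step.

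Selection of participants (Inclusion criteria) closes with the rule that "informed consent must be obtained at the inclusion".

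Clinical assessment methods (Selection, Actigraphy) confirms the order for the longest procedure: "each subject will be monitored for 7 days before being included in the study".

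**The concern.** The participants are healthy volunteers, and the protocol gives no care-related reason for a psychiatric symptom inventory, a week of movement monitoring or an overnight respiratory and leg-movement recording. The stated purpose is to check eligibility for this study. Two of the instruments do more than that. Criteria of assessment lists chronotype and habitual sleep patterns as secondary criteria, and Clinical assessment methods says that they come from the Horne and Ostberg questionnaire and the Basic Nordic Sleep Questionnaire. Some data meant for analysis are therefore also collected at this stage.

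A site that follows the schedule literally would run these procedures before the only signature the text provides for. The information is sensitive (psychiatric symptom scores, apnoea and leg-movement indices), and the order cannot be put right once a man has been tested. Men excluded on these results are in the weakest position, because the text gives them no consent step before the testing that excludes them.

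**Working it through.** No formula applies. The check is whether the sections give a consistent order, and where consent falls in it.

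**1. Are selection and inclusion distinct?** Yes. Experimental design names two visits with a period between them, and Experimental protocol gives each its own heading and its own list of tasks.

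**2. Which procedures fall before the inclusion visit?** Experimental protocol puts four questionnaires, 7 days of actimetry and 1 night of polygraphy under selection. The Actigraphy text independently places the 7 days before inclusion.

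**3. Where is consent?** It appears twice: once among the tasks of the inclusion step, and once as a rule at the end of the inclusion criteria. Both place it at inclusion. The text shown has no other consent step.

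**4. The resulting order:**

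| Step | Procedures | Consent in the text |
|---|---|---|
| Selection visit and period | 4 questionnaires, 7 days of actimetry, 1 polygraphy night | none stated |
| Inclusion visit | eligibility check, signature, cognitive tests, caffeine sensitivity questionnaire, blood | signed here |
| Driving sessions | night driving, ratings, saliva, recovery sleep | already signed |

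**5. Who is affected?** An included man must have met the criteria that rest on all the selection instruments, so he has been through all of them. Statistical considerations plans 48 men (24 + 24). Before the signature this gives:

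- questionnaires: 48 × 4 = 192
- actimetry: 48 × 7 = 336 person-days
- polygraphy: 48 × 1 = 48 nights

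Screen failures add to these figures by an unknown amount. The protocol gives neither their number nor the order in which the selection tests are applied.

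**6. What is not affected?** Blood and DNA sampling, the cognitive tests and the caffeine sensitivity questionnaire are listed in the same step as the signature, and driving comes later. Sample size, randomisation, endpoints and the planned models do not depend on the point.

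**The case against.** The strongest objection is that the consent pages and a design figure were not available, so a separate screening consent cannot be ruled out. That stands, and it limits what can be claimed. A reader might infer that psychiatric and sleep data are gathered with no consent at all; the document does not support that. It supports only that the one consent step it mentions comes after the selection procedures. The objection does not rescue the wording: if a screening consent exists, two sections still place consent at inclusion without mentioning it.

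A second objection is that the consent sentence, coming at the end of the inclusion criteria, may be a condition of entry rather than a visit timing, and that the inclusion step itself speaks of screening for eligibility, so the labels overlap. This is weaker. The experimental protocol lists signing as a task of the inclusion visit, and the Actigraphy text puts the monitoring before inclusion whatever the labels mean.

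A third objection concerns size. A reader might infer that every screened man undergoes the whole battery before consent. The protocol does not say that testing continues after a man has failed one criterion; someone excluded on a questionnaire score may never wear an actimeter or have polygraphy. The full burden is established for included men only.

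A fourth is that little follows for the analysis. This is correct. No analysis of screened-out men is described, and included men sign before any driving session. A reader might also infer that data from screen failures could not be kept or used; the document says nothing on that either way, and the point does not rely on it.

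**Conclusion.** The point holds as one of stated order. Two sections fix consent at inclusion, and two sections put the selection procedures before it, so this is not one loose word or a detail left to another document. The extent is all included men (48 as planned) for the full set of selection procedures, and screen failures for whatever part they had undergone.

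The conclusion rests on two assumptions: that sites follow the schedule as written, and that no earlier consent exists outside the text available. If the second fails, the practical harm falls away and what remains is wording that does not match practice.

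The point is ethical and procedural. It deserves correction before the first man is screened because a signature obtained later does not alter the order in which things were done.

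**What to change.** - **Study design (Experimental protocol):** make signing informed consent the first task of the selection step, before any questionnaire, actimeter or polygraph. At inclusion, replace the signing task with a confirmation that consent stands.
- **Selection of participants (Inclusion criteria):** change the closing sentence so that consent is required at the selection visit before any selection procedure.
- **If a screening consent is already in use:** state this in both sections, say which procedures it covers, and say what the signature at inclusion adds.

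The cost is small: two wording changes and the transfer of an existing step to an existing earlier visit. The downside is a short consent discussion with men who later fail screening. No endpoint, sample size, treatment or analysis changes.
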